#### 1.2. Data Analysis

The primary outcome is CRC screening completion (FIT or colonoscopy) within 4 months of initial outreach. We will conduct a chi-square analysis using Stata to compare arms 2 and 3 to arm 1 separately using intent-to-treat protocol. We will also compare arms 2 and 3 as a secondary analysis. We will quantitatively analyze the choice of screening test and evaluate the survey results by study arm. As exploratory analyses, we will evaluate response by practice location, age, gender, race/ethnicity, and income at the level of zip code.

Analysis will be conducted by blinded members of the research team at least four months after the last FIT is mailed.

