## **Method for Assigning Subjects to Groups**

Subjects will be randomly assigned Study ID numbers and then randomized to one of three study arms stratified by the two practice locations (University City and Valley Forge) using a computer-generated randomization algorithm. The research coordinator will record the randomization assignments on a master list which will be maintained by the research coordinator on a password protected computer in a locked office. The research coordinator and research assistants will assemble the mailings based on this master list.

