## **Study Design**

### 1.1 Design

Randomized: Subjects will be randomly assigned Study ID numbers and then randomized to one of three study arms stratified by practice location using a computer-generated randomization algorithm. The research coordinator will record the randomization assignments on a master list which will be maintained on a password protected computer in a locked office. The research coordinator and research assistants will assemble the mailings based on this master list.

Blinding: The investigators will be blinded to the randomization assignment. The research coordinator and research assistants will be unblinded. The blind may be broken for clinical care purposes.

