## Final Statistical Analysis Plan

**\*\*New changes from initial protocol notated in bold, parts removed from initial protocol notated in strikethrough**

### Analysis Plan

#### 1.1 Power and Sample Size

Approximately 900 potentially eligible subjects will be identified via a data abstraction by Penn Data Store. Through other projects in primary care practices at Penn Medicine we found the accuracy rate of the EMR algorithm to be approximately 75%. As such, we anticipate we will have enough patients to enroll 423 subjects (and randomize 141 into each arm). We estimate a base return rate for the colonoscopy only (control) arm to be 5%, and we will consider a meaningful increase in response rate to be ~~10~~ **11** percentage points for both the sequential choice and active choice arms as compared to control. This will be sufficient sample size to detect a ~~10~~ **11** percentage point increase in response rate using a two-tailed chi-square test with 80% power and a Type 1 error rate of .025, accounting for two pairwise comparisons with Bonferroni correction ( $.05/2 = .025$ ). ~~5% level of significance.~~

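### Randomization is stratified by practice but the primary chi-square is not; stratifying the test would match the design, at a gain of a fraction of a power point under the plan's assumptions

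*Supplement*

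**What the plan says.** In the Final Protocol, the section on assigning subjects to groups has subjects "randomized to one of three study arms stratified by the two practice locations (University City and Valley Forge) using a computer-generated randomization algorithm". Study Design 1.1 repeats this ("three study arms stratified by practice location using a computer-generated randomization algorithm"), and Phase 2 of the Procedures again mentions stratification. None of these sections says whether blocks or another restriction keep the arms balanced within a practice.

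The Final Statistical Analysis Plan, section 1.2, gives the primary test: "We will conduct a chi-square analysis using Stata to compare arms 2 and 3 to arm 1 separately using intent-to-treat protocol". The two Data analysis sections of the Final Protocol carry the same text. No stratified test, practice-adjusted model or stratified estimate is named for the primary outcome. Practice appears once: "As exploratory analyses, we will evaluate response by practice location, age, gender, race/ethnicity, and income at the level of zip code".

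Section 1.1 of the same plan sizes the trial at 141 per arm for 5% in control and an 11 "percentage point increase in response rate using a two-tailed chi-square test with 80% power", with a "Type 1 error rate of .025, accounting for two pairwise comparisons with Bonferroni correction".

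**The concern.** Practice is the only stratification factor. When arms are balanced within practice, differences in uptake between practices cannot enter the comparison of arms. The pooled chi-square still counts those differences in its variance. Its standard error is then a little too large, its true size falls below the nominal .025, and some power is given up.

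The stake is efficiency and agreement between analysis and design. The planned power is close to its 80% target, so a free gain is worth a look. It is also better to specify an adjustment for practice beforehand than to add it after results are known.

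**Working it through.** **Inputs from the Final Statistical Analysis Plan, section 1.1.** 141 per arm; control 5%; intervention 5% + 11 = 16%; two-sided alpha .025 per comparison, so z = 2.241; power 80%. (The Accrual section of the Final Protocol still shows 10 points and 5% significance; the analysis plan's figures are used here.)

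**Inputs that are assumed.** The documents give neither uptake by practice nor practice size. Both are varied below. Control rates are written as practice A/practice B.

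**Step 1: the plan's power.** With average rate .105, the pooled normal formula gives

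z(power) = [.11·√141 − 2.241·√(2·.105·.895)] / √(.05·.95 + .16·.84) = (1.306 − 0.972)/0.4265 = 0.784, so power is 78.4%.

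Simulating the Pearson chi-square itself gives 80.4%. The stated 80% is reproduced.

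**Step 2: large-sample size of the crude test under balance within practice.** With practice shares w and rates p,

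size = 2·[1 − Φ(2.241·√(V_total/V_within))], where V_total = p̄(1 − p̄) and V_within = Σ w·p(1 − p).

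For 2%/8% in equal practices, V_total = .05·.95 = .0475 and V_within = .5·.02·.98 + .5·.08·.92 = .0466. The ratio V_within/V_total is .981 and the size is .0236. For 3%/7% it is .0244, for 1%/9% it is .0226, and for equal rates exactly .025.

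**Step 3: simulation at the planned 5% average control rate.** 400,000 trials per row, 70 + 71 per arm by practice, crude chi-square against Cochran-Mantel-Haenszel (CMH) without continuity correction. Power is for +11 points in both practices.

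| Control rates | Size, crude / CMH | Power %, crude / CMH | Gain, points |
|---|---|---|---|
| 5%/5% | .0233 / .0233 | 80.43 / 80.38 | about 0 |
| 3%/7% | .0223 / .0224 | 80.37 / 80.43 | 0.1 |
| 2%/8% | .0215 / .0219 | 80.26 / 80.52 | 0.3 |
| 1%/9% | .0206 / .0218 | 80.47 / 81.03 | 0.6 |
| 0%/10% (limit) | .0200 / .0243 | 80.53 / 81.51 | 1.0 |

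The simulation standard error is √(.025·.975/400,000) = .0002 for size and √(.8·.2/400,000) = 0.06 points for each power.

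**Step 4: source of the size shortfall.** With identical practices both tests already sit at .0233, because only about 141·.05 = 7 events are expected per arm. At 2%/8% the crude shortfall is .025 − .0215 = .0035, of which CMH recovers .0219 − .0215 = .0004. At 1%/9% it recovers .0012 of .0044. The rest is discreteness. Only in the limiting 0%/10% case does CMH recover most of the shortfall (.0043 of .0050).

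**Step 5: effects that also differ by practice.**

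| Control | Intervention | Power %, crude / CMH | Gain, points |
|---|---|---|---|
| 2%/8% | 10%/22% | 80.7 / 81.4 | 0.7 |
| 2%/8% | 8%/24% | 80.9 / 81.9 | 1.0 |
| 1%/9% | 6%/26% | 81.2 / 82.9 | 1.7 |

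The average effect is still 11 points, but it is +8/+14, +6/+16 and +5/+17 by practice. A common 3.2-fold ratio is steeper and gives 81.1 / 82.5 at 2%/8% and 81.7 / 84.0 at 1%/9%.

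**Step 6: unequal practices.** With a 70/30 split and +11 points in both, the gain is 0.1 (3%/7%), 0.3 (2%/8%) and 0.6 points (1%/9%).

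**Step 7: no balance within practice.** With simple randomization inside each practice, the crude size is .0250 at 5%/20% and .0255 at 10%/30%, so the conservatism disappears. CMH still gains power in the three scenarios of step 5: 80.4 / 81.1, 80.3 / 81.4 and 80.5 / 82.5.

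**The case against.** The strongest answer is that nothing here threatens validity. The crude chi-square neither biases the risk difference nor inflates the type I error; the sample size and the analysis rest on the same test; and response by practice is prespecified, if only as exploratory. All of that stands, and it limits the point to efficiency.

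Three stronger readings are tempting, and the documents do not support them.

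- A reader might infer that the crude test is conservative whenever the practices differ. That needs arms balanced within practice. The documents state stratification but no blocking, and step 7 shows about nominal size without balance.
- A reader might infer a marked loss of size from examples such as 5%/20% (.0221 crude, .0244 CMH) or 10%/30% (.0208, .0246). Those average 12.5% and 20% uptake, against the planned 5% in control.
- A reader might infer that the trial falls short of 80% power because the strata are ignored. In every row of steps 3 and 5 the simulated crude test keeps at least 80%. What is lost is an available gain.

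Nor do the documents show that the two practices differ in uptake at all; if they do not, stratifying changes nothing. What survives the objection is that the stratified test has essentially no cost and gains a little if they do differ.

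**Conclusion.** The mismatch is real: randomization is stratified by practice and the primary test is not. Its consequence is minor. With a 5% average control rate, +11 points in both practices and control rates between 5%/5% and 1%/9%, a stratified test gains about 0 to 0.6 points of power. Gains of about 0.7 to 1.7 points need an effect that also differs by practice, as in the first table of step 5, and steeper assumed contrasts carry it further. Slight conservatism of the crude test is conditional on balanced allocation within practice and on uptake that differs between practices. All practice-specific rates are assumptions. This is a low-priority improvement, not a fault in the validity of the primary analysis.

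**What to change.** In section 1.2 of the Final Statistical Analysis Plan, and in the matching Data analysis sections of the Final Protocol, make the primary test of each of arms 2 and 3 against arm 1 a Cochran-Mantel-Haenszel test stratified by practice, at two-sided .025. Report a Mantel-Haenszel risk difference with a 97.5% confidence interval for each comparison, which also matches the Bonferroni level. Keep the crude chi-square as a supportive analysis.

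The cost is about one sentence and standard Stata commands. Practice is needed to randomize, so it is known for every subject, and the sample size need not change.

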**Key Exclusion Criteria**

1. Has had prior colonoscopy within 10 years, sigmoidoscopy within 5 years, and FOBT/FIT within twelve months of the chart review (We will exclude patients who self-report undergoing any of the above procedures)
2. Has a history of CRC
3. Has a history of other GI cancer
4. Has history of confirmed Inflammatory Bowel Disease (IBD) (e.g. Crohns disease, ulcerative colitis) Irritable bowel syndrome does not exclude patients.
5. Has history of colitis other than Crohns disease or ulcerative colitis
6. Has had a colectomy
7. Has a relative that has been diagnosed with CRC
8. Has been diagnosed with Lynch Syndrome (i.e. HNPCC)
9. Has been diagnosed with Familial Adenomatous Polyposis (FAP)
10. Has iron deficiency anemia
11. Has history of lower GI bleeding
12. Has metastatic (Stage IV) blood or solid tumor cancer
13. Has end stage renal disease
14. Has had congestive heart failure
15. Has dementia
16. Has liver cirrhosis
17. Has any other condition that, in the opinion of the investigator, excludes the patient from participating in this study

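### The crude primary chi-square is valid and adequately powered, but leaves practice, age and gender unused; a prespecified adjusted score test would hold the error rate and might add 0 to about 1.7 points of power

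*Supplement*

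**What the plan says.** Final SAP, section 1.2 Data Analysis, on the primary outcome of screening completion within 4 months: "We will conduct a chi-square analysis using Stata to compare arms 2 and 3 to arm 1 separately using intent-to-treat protocol". The final protocol says the same under both Statistical Considerations and Analysis Plan. No covariate enters this comparison and no adjusted estimate is planned.

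The same section lists baseline factors for exploratory evaluation of response only: "practice location, age, gender, race/ethnicity, and income at the level of zip code". The final protocol, under Method for Assigning Subjects to Groups and under Study Design, stratifies randomization by practice location (two sites). The stratum therefore shapes the allocation but not the primary analysis.

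Final SAP, section 1.1 Power and Sample Size, plans 423 subjects (141 per arm), a control rate of 5%, an increase of 11 percentage points, a "two-tailed chi-square test with 80% power" and a "Type 1 error rate of .025, accounting for two pairwise comparisons with Bonferroni correction".

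**The concern.** When baseline values predict a binary outcome, a test that conditions on them is usually somewhat more powerful than a crude one, and it allows for chance imbalance in those values. Two features make the question worth asking here. The design sits on its 80% line with little to spare, and few events are expected: 141 × 0.05 ≈ 7 in the control arm and 141 × 0.16 ≈ 23 in a choice arm, about 30 per comparison. Practice and age must be known at enrollment (stratum and eligibility criterion), and gender is listed for analysis, so using them needs no new data. At stake is a small amount of power and precision, not the validity of the trial's conclusion.

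**Working it through.** **Inputs.** From final SAP 1.1: n = 141 per arm, p1 = 0.05, p2 = 0.05 + 0.11 = 0.16, two-sided alpha 0.025, so the critical value is z = 2.2414. Covariate strengths are not in the documents and are assumed below.

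**Step 1: reproduce the stated 80%.** Pooled normal formula: power = Φ[(d − z·SE0)/SE1].
- d = 0.11; mean rate 0.105.
- SE0 = √(2 × 0.105 × 0.895 / 141) = 0.03651, so z·SE0 = 0.08183.
- SE1 = √((0.05 × 0.95 + 0.16 × 0.84) / 141) = 0.03592.
- Power = Φ(0.02817 / 0.03592) = Φ(0.784) = 78.4%.

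Exact enumeration of the uncorrected Pearson chi-square over both binomial distributions gives 80.3%, with an exact size of 0.023 when both rates are 5%. The plan's figure reproduces.

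**Step 2: does the adjusted test keep its level?** The test is the score test for arm, with the logistic covariate model fitted without arm. In simulations of 20,000 trials per scenario with three covariate terms and both rates at 5%, type I error was 0.024 to 0.026 against a nominal 0.025; the crude test ran at 0.022 to 0.024. A separate simulation with practice, age and gender (8,000 trials per scenario) gave about 0.021 to 0.027. The Monte Carlo standard error at 8,000 trials is √(0.025 × 0.975 / 8,000) ≈ 0.0017, so that range is compatible with the nominal level.

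**Step 3: what power is gained?** Marginal rates were held at 5% and 16%.

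| Assumed covariate strength | Crude | Adjusted | Gain (points) |
|---|---|---|---|
| No predictive value, three terms fitted | 80.2% | 80.3% | 0.1 |
| Age (odds ratio 1.3 per SD) and gender (odds ratio 1.5), third term without effect; R² about 1% | 80.1% | 80.5% | 0.4 |
| Practice, age and gender, moderate | – | – | about 0.5 |
| Practice, age and gender, stronger | – | – | about 1.7 |

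The first two rows come from the 20,000-trial simulation and the last two from the 8,000-trial one.

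**Step 4: cross-check.** Adjustment shrinks both standard errors by roughly √(1 − R²), where R² is the share of outcome variance the covariates explain. In the formula of step 1:
- R² = 1%: 78.8%, a gain of about 0.45 points.
- R² = 3.8%: the factor is √0.962 = 0.981, and power is Φ[(0.11 − 0.0803)/0.0352] = Φ(0.844) = 80.1%, a gain of 1.7 points.

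So the upper figure needs the three covariates together to explain nearly 4% of the variance. On the sample-size scale, the pooled formula asks for 147 per arm unadjusted, against 147 × 0.99 = 145.5 and 147 × 0.962 = 141.4. The gain is worth between 1 or 2 and about 6 subjects per arm.

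**The case against.** The strongest reply is that nothing in the plan is wrong. The chi-square is valid under randomization, its type I error already covers chance imbalance, it is the test on which the power statement rests, and it delivers that power. A crude primary test for a simple binary endpoint is a legitimate choice, and the documents offer no evidence that practice, age or gender predict uptake. All of that stands, and it makes this a suggestion rather than a defect.

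Two stronger readings are tempting. First, a reader might infer from the pooled 78.4% that the trial misses its power target and needs adjustment to reach it. The exact calculation gives 80.3%, so it does not.

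Second, a reader might infer from exclusion criterion 1, "Has had prior colonoscopy within 10 years, sigmoidoscopy within 5 years, and FOBT/FIT within twelve months of the chart review", that prior screening is also on hand and could yield a larger gain. In the 20,000-trial simulation, adding prior screening with an assumed odds ratio of 4 to age and gender did move power from 80.1% to 82.7%. But the criterion is an eligibility check that removes people with in-window tests. Nothing says that older, lapsed tests are recorded. The question about ever having been screened (Appendix A) goes only to the telephone sub-sample of 90, about 6 months after outreach, so it is not a baseline value for all 423. The documents support no figure of that size.

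One further caution holds: only the test was simulated. With about 7 expected control events, the coverage of an interval for a standardized risk difference has not been examined here.

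**Conclusion.** The point holds as an optional efficiency gain of minor importance. The crude test is sound and reaches its stated power. Adjusting for practice, age and gender holds type I error near .025, costs no power in the scenarios examined even when the covariates are uninformative, and gains about 0.5 points with moderate effects and up to about 1.7 with stronger ones. Every figure above zero rests on assumed covariate strengths, and the true gain may be negligible. Practice has the clearest claim to inclusion because the randomization is stratified on it.

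**What to change.** In final SAP 1.2, prespecify as the primary test for each choice arm against control, at alpha .025, the score test for arm in a logistic model with practice location, age (linear) and gender. That is 3 covariate parameters for about 30 expected events, or about 10 events each; the list should not grow much beyond this. Report a covariate-standardized risk difference with a confidence interval, name the interval method, and check its coverage at the expected event counts before adopting it. Keep the crude chi-square as a supportive analysis, and leave race/ethnicity and zip-code income exploratory. Make the same edit in the two Data analysis sections of the final protocol.

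Earlier colorectal screening could be added only if it was abstracted at chart review for all subjects; otherwise it would need a fresh abstraction.

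The cost is SAP wording and a few lines of Stata, with no new data or subjects. The downsides are a slightly less simple primary analysis and a gain that may turn out to be nil. The change has to be fixed before outcomes are analyzed by arm; the modifications log shows that the analysis plan was itself revised before any analysis began.

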## Summary of Statistical Analysis Plan Modifications

Before analysis, we felt it necessary to revisit outcomes and provide a more detailed/thorough analysis plan to ensure both were as complete as possible. The analysis plan was updated to be more descriptive of the specific comparisons that would be made, to include communication modality and demographics.

## Appendix A – Final Survey Instrument

We're calling from <Penn Medicine Pt's Practice> to ask you a few questions about screening for colon cancer. The questions shouldn't take more than 10-15 minutes to complete, and we value your input on this important subject. There are no wrong answers and your responses could help us better care for our patients in the future.

Do you have a few minutes now to answer a few questions?

**1) What have you heard about getting screened for colon cancer? Whether you've had experience with it firsthand or heard about it from someone else, anything you've heard is helpful to us.** (Probe for awareness of screening options, social influence, barriers, frequency, cost, ease, any past screening/non-screening experiences)

**2) Prior to November 2017, had you ever been screened for colon cancer before? Y/N**

If N: question 3

If Y: which test?

If Y: do you remember when?

If Y: do you remember where it was done?

**3) In November 2017, we mailed you an invitation to participate in colon cancer screening. What was your experience with that invitation?**

(if no recollection/didn't receive it, skip to question 5)

**4) Our records show that you didn't complete FIT/Colonoscopy after receiving that invitation. Don't worry – you're not alone, many people didn't! Can you tell me about how that invitation helped you think about getting yourself screened for colon cancer? What are some of the reasons you decided not to get it done? What would facilitate you getting screened in the future?**

or

Our records show that you completed FIT/Colonoscopy after receiving that invitation – that's fantastic! **Can you tell me about how that invitation helped you think about getting yourself screened for colon cancer? What are some of the reasons you decided to get it done?**

- a. Follow-up: **Good or bad, we'd love to hear your screening story so we can capitalize on our strengths and improve where we fall short. Can you tell us about this colon cancer screening experience?** (Convenience/ease, prep, time it took, confidence in process/results, repeat, what would you tell others about it?)

113 5) The FIT test is an at-home screening test for colon cancer where you send a swab of stool to the lab to  
114 test for blood. Most doctors want their patients who are 50-75 years old to either do this test once per  
115 year, or get a colonoscopy once every ten years. **In the future, would you prefer to have a colonoscopy**  
116 **every 10 years or take a FIT every year?**

- 117 a) FIT
- 118 b) Colonoscopy
- 119 c) No preference
- 120 d) Prefer not to be screened

121  
122 6) Can you tell us more about why FIT/Colonoscopy is your preference?

123  
124 7) What would be the most helpful thing Penn Medicine could do to help ensure you get screened for  
125 colon cancer regularly?

126  
127 Thank you for taking the time to give us your input, we appreciate it!

128 If you have any questions about this call, the FIT kit, colonoscopy or colon cancer screening in general, please  
129 call us at XXX-XXX-XXXX or speak with your Doctor.

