### Study Instruments

The primary endpoint being evaluated is the rate of participation in colorectal cancer screening between the two intervention arms (Sequential Choice, Active Choice) versus the control arm (colonoscopy only). The FIT is a well validated tool for colorectal cancer screening and is one of the screening modalities recommended by the USPSTF. The control arm will be sent a letter inviting them to schedule screening colonoscopy directly through the Gastroenterology Call Center. If not scheduled within 4 weeks, subjects will receive a mailed reminder to call to schedule. The Sequential Choice arm will be sent the same initial outreach as the control arm. If not scheduled within 4 weeks, subjects will receive a mailed reminder including the call center number as well as the option to complete a FIT kit mailed along with the reminder. The Active Choice arm of the study will be sent a letter offering the choice of Colonoscopy or completion of the FIT kit included with the initial mailing. If subjects in this group have not either scheduled colonoscopy nor completed FIT within 4 weeks, they will receive a mailed reminder to call to schedule colonoscopy or to complete the original mailed FIT.

A sub-sample of 90 subjects will be called to complete a questionnaire over the phone ~~4~~**beginning approximately 6** months after initial outreach was mailed. ~~The subjects will be asked to confirm their eligibility (e.g. that they had not had CRC screening within the USPSTF CRC screening guidelines) and provide additional demographic and socioeconomic information so that we can better understand what populations, if any, may have differential response rates. We will also ask them~~ **The subjects will be asked to explain their experience with CRC screening prior to our initial outreach (November 2017), as well as about their perception of the impact and design of CRC screening outreach. Additional questions will probe for potential barriers to screening participation and ways to improve participation in the future.** ~~Demographic and socioeconomic questions are modified from demographic questions on the Behavioral Risk Factor Surveillance System survey, administered by the Centers for Disease Control and Prevention. See attached sub-sample questionnaire.~~

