### Group Modifications

For subjects in the Control (Colonoscopy only) arm of the study, the post outreach phone questionnaires will not include questions regarding mailed FIT.

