### 1.6 Secondary Outcome Variable(s)

The secondary outcome is the choice of screening test between FIT and colonoscopy.

Additional outcomes include demographic and socioeconomic characteristics of subjects who participate, as well as exploratory qualitative data regarding experience with the different outreach methodologies. Additional outcome is the percentage of FIT screening results that are positive, percentage of those positive FIT tests that receive follow-up diagnostic colonoscopy, and percentage of colonoscopies that find adenomas, advanced adenomas, and cancer.

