**Outreach & Follow-up - Phase 3:** Initial outreach letters will be sent to subjects. In the control arm the outreach will include a phone number to the VIP colonoscopy scheduling center. For the sequential choice arm, subjects will receive the same message as those in the control arm, indicating they are overdue for screening and including a phone number to the VIP screening scheduling center. For the active choice arm, subjects will receive both a mailed FIT kit and the option to call and schedule colonoscopy at the same time. After four weeks, a reminder letter will be sent to all subjects in all three arms who did not either schedule a colonoscopy appointment or complete and return a FIT kit. Subjects in the Control arm will receive a reminder letter that includes the same phone number to schedule colonoscopy. Subjects in the sequential choice arm will receive a second letter containing the phone number to the VIP screening scheduling center as well as a FIT kit. The active choice arm will receive a reminder that includes both the phone number to the VIP screening scheduling center and a reminder that they may alternatively complete the FIT that was initially mailed. The Research Coordinator and Research Assistants will be responsible for assembling the mailings. FIT kits will include a tube in which to deposit the stool sample, directions on how to collect and mail the sample, a letter about CRC screening, a lab requisition form, and a pre-paid return envelope.

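### The final interview asks directly only about the November 2017 first letter, so it cannot reliably separate Sequential Choice patients' experience of outreach from control's

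*Supplement*

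**What the plan says.** **The interview.** Appendix A (Final Survey Instrument) is one script for all arms. Question 3 asks: "In November 2017, we mailed you an invitation to participate in colon cancer screening. What was your experience with that invitation". A patient who does not recall that letter, or did not receive it, goes straight to question 5. Both branches of question 4 (screened, not screened) refer back to the same invitation. Follow-up 4a asks openly about the screening experience. Questions 5 and 6 ask about future preference between FIT and colonoscopy.

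**Which mailing this is.** Under Study Instruments, the Final Protocol says interviewees will describe their "experience with CRC screening prior to our initial outreach (November 2017", which fixes November 2017 as the month of the first mailing.

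**What each arm was sent.** "The Sequential Choice arm will be sent the same initial outreach as the control arm". Sequential Choice patients who have not scheduled by four weeks are then sent a reminder that repeats the call center number and encloses a FIT kit they may use instead. Procedures, Phase 3, agrees: "Subjects in the sequential choice arm will receive a second letter containing the phone number to the VIP screening scheduling center", together with a FIT kit. In Active Choice the offer is "completion of the FIT kit included with the initial mailing".

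**What the interview is for.** Section 1.6 lists "exploratory qualitative data regarding experience with the different outreach methodologies" among the additional outcomes, and section 1.2 of the Final Statistical Analysis Plan evaluates survey results by study arm. Group Modifications adds that, for control, "the post outreach phone questionnaires will not include questions regarding mailed FIT".

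**The concern.** Control and Sequential Choice differ only from the second mailing onward, and the script never mentions that mailing. Interviewees in both arms are asked about what is in effect the same colonoscopy letter, while Active Choice interviewees are asked about a mailing that did contain the kit. The by-arm reading is therefore lopsided: question 3 covers the FIT offer in Active Choice and misses it in Sequential Choice.

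At stake is the exploratory account of how patients experienced being offered FIT after colonoscopy, compared with being offered both at once or colonoscopy alone.

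**Working it through.** The point rests on the text; arithmetic enters only for the number of interviews and the dates.

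**1. Interview yield.** Inputs from Administration of Surveys and/or Process: 90 selected, about 50% reached. 90 × 0.50 = 45, and 45 / 3 = 15 per arm. This reproduces the plan's own figures of 45 and 15.

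**2. Could the November invitation mean the reminder?** The reminder follows the first letter by four weeks (28 days).
- First letter on 1 November: reminder on 29 November.
- First letter on 30 November: reminder on 28 December.
- The reminder falls in November only if the first letter went out on 1 or 2 November.

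With the protocol's own dating of the initial outreach, question 3 points to the first letter.

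**3. Mailings against the script** (Final Protocol and Appendix B):

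| Arm | First mailing | Four-week reminder | FIT offer covered by question 3? |
|---|---|---|---|
| Control | Colonoscopy letter | Same letter | Not applicable |
| Sequential Choice | Colonoscopy letter; as printed it lacks only the word *today* in the last line of the control letter | Colonoscopy or enclosed FIT kit | No |
| Active Choice | Colonoscopy or enclosed FIT kit | Text repeats the first letter; kit already sent | Yes |

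**4. Paths of a Sequential Choice interviewee who was sent the kit.**
- *Recalls the November letter and returned a FIT.* Question 4 asks how that letter helped, and 4a asks how the test went. The FIT experience is recorded, but credited to a letter that did not offer FIT.
- *Recalls the November letter and was not screened.* Question 4 asks why not. The kit comes up only if the patient raises it.
- *Recalls only the later package.* Taken literally, the answer to question 3 is no recollection, and the skip drops question 4 and 4a, the items on why the patient did or did not get screened after outreach. If the patient instead answers about the later package as though it were the November letter, nothing in the script lets the interviewer tell the two apart.
- *Recalls nothing.* The skip works as intended.

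Interviews begin about six months after the first mailing, so mixed or partial recall is plausible. The documents give no figure for it.

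**5. Against the stated purpose.** A by-arm account of outreach experience needs answers tied to the contact that distinguishes the arm. For Sequential Choice the script supplies that link only by chance.

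**The case against.** Four arguments carry weight.

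- **FIT is not absent from the script.** Question 1 probes awareness of screening options, both branches of question 4 name FIT, 4a probes convenience, time and confidence, and the closing line mentions the kit. This stands: a reader might infer that the interview says nothing about the sequential offer, and that goes too far. What is missing is a direct prompt and the correct attribution.
- **Open questions were chosen on purpose.** The modifications log describes a guided interview meant to gather a broader set of experiences. This stands as a reason against a closed questionnaire. It does not count against an open prompt that names the right mailing.
- **Recall limits what a prompt can achieve.** The printed reminders do not call themselves reminders, and those for control and Active Choice repeat the text of the first letter. Separating the two mailings six months later is hard in those arms. This stands, but it applies least to Sequential Choice, whose reminder differs visibly.
- **Group Modifications is not breached.** It excludes mailed-FIT questions for control. A reader might infer that it promises them for the other arms, but it does not say so. At most the sentence has little left to act on in the final script.

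Two stronger readings also fail. A reader might conclude that the offer defining Sequential Choice goes unevaluated. The randomized primary outcome, the choice-of-test outcome and the planned comparison of arms 2 and 3 all evaluate it. A reader might also take the 5% base return rate and compute 15 × (1 − 0.05) = 14.25, or about 14 of 15 Sequential Choice interviewees first offered FIT in the unmentioned mailing. The 5% is an assumed control rate behind a four-month completion outcome. The reminder depends on scheduling by week four, and people can schedule without completing, so 5% is no ceiling on scheduling. Patients reached by phone may also differ from all those randomized.

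**Conclusion.** The gap is real and modest. The final interview asks directly only about the first letter, has no prompt on the reminder or the kit enclosed with it, and can route a patient who recalls only that package past question 4 and 4a. As written, it cannot reliably separate the outreach experience of Sequential Choice from that of control.

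The size is bounded by about 15 expected Sequential Choice interviews. How many of those patients were sent the kit, or recall only the later package, cannot be derived from the documents. The conclusion assumes that interviewers follow the script and its skip rule as printed; improvised probing would narrow the gap. The primary outcome, the choice-of-test outcome and their analyses are not affected.

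**What to change.** Make three changes to Appendix A:

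1. After question 3, add one open-ended prompt on the later mailing for patients who were sent it. Word it by arm: Sequential Choice names the FIT kit enclosed with that mailing; Active Choice names the kit in the first mailing; control carries no FIT wording, in line with Group Modifications.
2. In question 4, refer to the mailings in the plural instead of the single invitation.
3. Apply the skip to question 5 only when the patient recalls no mailing at all.

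The interviewer needs the arm and whether a reminder was sent. The cost is a few script lines, a minor amendment to patient materials and a slightly longer call. Call length deserves a look, since the protocol anticipates 10 minutes and the script already tells patients 10 to 15. Answers to the new prompt will still be limited by recall at about six months, mostly in control and Active Choice, and should be reported as exploratory.
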